Some children still require additional surgical intervention due to remaining velopharyngeal insufficiency (VPI) after primary palatoplasty. VPI is an anatomical deficiency where the velopharyngeal port cannot adequately close to fully separate the oral and nasal cavities during speech and/or swallowing. VPI results in hypernasality, nasal air emission, and/or weak pressure consonants. Children with VPI are also at greater risk of compensatory articulation errors, which are abnormal, learned sound substitutions [8]. All these speech issues impact a person’s ability to communicate effectively. Rates of VPI range widely among hospitals, regions, and countries between 13% and 40% [9,10]. Inability of the initial palate repair surgery to address VPI places children at risk of long-term psychosocial challenges and increases the likelihood of additional costly interventions [11-13]. Even children with otherwise successful repairs often require speech therapy, with 34% to 68% exhibiting cleft speech characteristics [14-16].

Despite advances in surgical training and multidisciplinary cleft care, the incidence of speech disorders after repair has remained high for decades [17]. The timing and technique of primary palatoplasty have been shown to influence surgical outcomes [18]; however, these do not fully explain why some children continue to experience speech difficulties. Earlier repairs tend to result in reduced hypernasality and improved consonant production [14,19], but not all studies agree, with some reporting no clear age effect in secondary VPI surgery [3]. Recent prospective evidence further supports an association between timing and early speech sound development, particularly oral stop consonant production. A recent study of 113 infants with repaired cleft palate revealed that at least one oral stop was evident in the consonant inventory for 84% of children at 16 months, 71% produced 2 or more different stops, and only 7% produced all 6 stop consonants [20]. This represents a gap in the literature supporting early surgical and speech outcomes for children with cleft palate.

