### Aims of This Study

In summary, recent studies quantifying the velopharynx in children have generally examined anatomy and physiology in isolation [35], and many have relied on cross-sectional designs [15,32]. Few have tracked both anatomical and functional measures at 2 time points within the same individual. Multidimensional data before and after palatoplasty are crucial for understanding how palate repair influences both velopharyngeal structure and function. These individualized assessments are key for translating basic science findings into patient-specific surgical planning and targeted interventions. This protocol aims to take an essential step toward precision medicine in infants with cleft palate.

This study combines nonsedated MRI–based anatomical assessment with functional speech measurements in the same infants before and after palatoplasty. By linking patient-specific anatomy before and after palate repair to early speech outcomes, we aim to establish data-driven criteria for individualized surgical planning and targeted speech monitoring. This approach addresses a critical gap by providing quantitative, objective measures of surgical success and velopharyngeal development, moving beyond subjective assessment. Ultimately, these findings may lead to work that reduces persistent speech deficits, prevents multiple surgeries, and lessens the associated psychosocial and financial burden of cleft palate. Specifically, this study has two primary aims:

To establish which presurgical anatomical variables are predictive of surgical procedure selection based on perceptual assessment of intraoperative tension for palate repair (hypothesis: preoperative cleft width and LVP muscle length are predictive of surgical procedure selection based on intraoperative tension of palatal tissue)To determine which postsurgical anatomical features are associated with the greatest diversity in oral stop consonant production at 18 months in children with repaired cleft palate (hypothesis: a longer velum, greater effective velopharyngeal ratio, and continuity of the LVP muscle are associated with greater diversity of oral stop consonants by 18 months but not with procedure type)

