### Evaluation Outcomes

The primary outcomes correspond to the 2 study aims. For aim 1, the primary outcome is the type of surgical procedure performed (IVV or DOZ with or without adjunct tissue use) predicted by preoperative anatomical variables, namely, cleft width and LVP muscle length. For aim 2, the primary outcome is the diversity of oral stop consonants produced at 18 months, serving as a functional measure of velopharyngeal competence. Secondary outcomes include additional anatomical measures (effective velar length, effective velopharyngeal ratio, and LVP muscle continuity) and developmental and language scores. Anatomical variable definitions are outlined in Table 1. Exploratory tertiary outcomes will examine modifiers of anatomy and speech, including sex, demographic characteristics, tympanometry results, and other developmental assessments. Missing data will be imputed (when appropriate) or addressed using pairwise deletion. Additionally, data may be analyzed cross-sectionally to meet the study aims.

**Table 1 table1:** Anatomical variables and corresponding definitions as obtained from magnetic resonance imaging for aims 1 and 2.

Variable	Definition
Cleft width	Distance between the lateral margins of the cleft at the widest point
Effective VP^a^ ratio	Effective velar length/pharyngeal depth
Effective velar length	Length of the velum from the posterior hard palate to the LVP^b^ muscle
LVP muscle angle of origin	Interior angle created by the lines drawn to measure distance between the origin points and LVP muscle length
LVP muscle continuity	Whether the LVP muscle is continuous through the midline (yes or no)
LVP muscle length	Length of the LVP muscle along one side from origin to insertion
Origin-origin distance	Distance between the points of origin of the LVP muscle
Pharyngeal depth	Distance from the posterior hard palate to the posterior pharyngeal wall at the palatal plane
VP ratio	Total velar length/pharyngeal depth
Velar insertion distance	Distance between the locations where the bilateral LVP muscle bundles insert into the body of the velum (ie, repaired velar width)
Velar length	Length of the velum from the posterior hard palate to the tip of the uvula
Velar thickness	Distance from the velar knee to the velar dimple

^a^VP: velopharyngeal.

^b^LVP: levator veli palatini.

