### Statistical Analysis

All participants with data at the relevant time points will be included in each analysis. The primary outcome will be evaluated using binomial logistic regression to determine how preoperative anatomical variables predict surgical procedure selection, controlling for sex, race, and cleft type. Principal component analysis may be applied to reduce dimensionality among anatomical predictors. The secondary outcome will be assessed using a 2-way analysis of covariance examining the effects of surgical type and number of oral stops on postsurgical anatomical measures, controlling for sex, cleft type, and developmental and language scores.

To ensure scientific rigor, intrarater and interrater reliability will be calculated for both MRI and speech measures. Independent raters will measure MRI scans and consonant productions following completion of a structured reliability training protocol to enhance measurement accuracy and precision. This training will consist of a guided review of the velopharyngeal MRI and speech literature, a detailed study of relevant cleft MRI anatomy and speech characteristics, and repeated practice measurements of both typical children and those with cleft palate until a predetermined level of agreement is reached. Each measurement training cycle will be followed by discussion-based debriefing and troubleshooting. The primary rater will measure all samples, whereas a second rater will measure a randomly selected 10% of the samples to calculate interrater reliability. The primary rater will rerate a random selection of 10% of the samples to calculate intrarater reliability.

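### Aim 2 names oral stop diversity as its primary outcome, but the only Aim 2 model makes anatomy the response and stops an explanatory term

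*Protocol article*

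**What the plan says.** All references are to the protocol article.

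- **Aims of This Study.** Aim 2 is to "determine which postsurgical anatomical features are associated with the greatest diversity in oral stop consonant production at 18 months". Its hypothesis is that "a longer velum, greater effective velopharyngeal ratio, and continuity of the LVP muscle are associated with greater diversity of oral stop consonants by 18 months", and it adds that procedure type is not expected to show an association.
- **Evaluation Outcomes.** "For aim 2, the primary outcome is the diversity of oral stop consonants produced at 18 months". Anatomy appears one level down: "Secondary outcomes include additional anatomical measures (effective velar length, effective velopharyngeal ratio, and LVP muscle continuity"). Table 1 defines LVP continuity as "Whether the LVP muscle is continuous through the midline (yes or no").
- **Statistical Analysis.** The primary outcome is analysed by the Aim 1 logistic regression. What the section calls the secondary outcome gets a 2-way ANCOVA, described as "examining the effects of surgical type and number of oral stops on postsurgical anatomical measures". The adjustment covers sex, type of cleft and the scores for development and language. No other Aim 2 model is given.
- **Abstract, Methods.** ANCOVA is named for the association between anatomy and stop diversity, without saying which side is the response.

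**The concern.** The aim and the outcome list put speech on the response side and anatomy on the explanatory side. The analysis paragraph swaps them. One of the two primary outcomes is then left with no model in which it is the response.

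Three things are at stake whatever the coding of stops:

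1. The question is *which* features matter. Separate models, one per anatomical measure, cannot separate a feature that is related to stops from one that is merely correlated with such a feature.
2. The difference in stop diversity between the two procedures is not estimated. The model's procedure term is a difference in anatomy.
3. LVP continuity is one of three hypothesised features and is binary. As an ANCOVA dependent variable it cannot meet the normal, constant-variance error assumption. As a predictor it would cause no difficulty.

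A fourth issue depends on coding. Calling the model 2-way, with surgical type and number of stops as the two effects, suggests that stops are a categorical factor, which would be very sparse at this sample size.

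**Working it through.** The article states no power or precision figure for Aim 2, so there is none to reproduce.

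**1. Roles of the variables**

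| Section | Response | Explanatory |
|---|---|---|
| Aims of This Study, Aim 2 | stop diversity | anatomical features |
| Evaluation Outcomes, Aim 2 primary | stop diversity | not stated |
| Statistical Analysis, ANCOVA | anatomical measures | surgical type, number of stops |

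The label changes too: stop diversity is primary in Evaluation Outcomes, while the only model that includes it is attached to the secondary outcome.

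**2. Cell count if stops are a full factor**

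- Levels: Background reports that "only 7% produced all 6 stop consonants" in a cited cohort, so the count runs from 0 to 6, giving 7 levels.
- Cells: 2 procedures × 7 = 14.
- Children: the target is 30; 39 enrolled with 30% attrition leaves 39 × 0.7 = 27.3.
- Average per cell: 27/14 = 1.9 to 30/14 = 2.1.
- Parameters: 14 cells + 1 (sex) + 1 to 3 (cleft type, assuming 2 to 4 categories) + 2 to 6 (scores, assumed) = 18 to 24. Residual degrees of freedom at n = 30 are 12 down to 6.

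**3. How much the coding of stops matters**

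The cited cohort at 16 months had 84% with at least one stop, 71% with two or more and 7% with all six. That gives 16% with none, 84 − 71 = 13% with one, and 71 − 7 = 64% with two to five, assumed evenly spread. With an assumed latent correlation of 0.5 between one anatomical measure and stops, and covariates like those planned, simulation at n = 27 gives:

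| Model | Power for that measure |
|---|---|
| Anatomy on stops, 7-level factor | 29% |
| Anatomy on stops, three groups (0–1, 2–3, 4–6) | 43% |
| Anatomy on stops, one linear term | 64% |
| Stops on anatomy, linear | 64% |

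With the full factor, at least one of the 14 cells is empty in about 93% to 95% of simulated studies at n = 27. The last two rows agree because, with the same covariates, the partial *t* statistic is the same in both directions. In one simulated dataset it was 0.266 both ways for a continuous feature and −2.365 both ways for a binary one. The power loss therefore comes from coding, not from the reversal.

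**4. What one-at-a-time models miss**

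By Table 1, velar length and effective velar length both start at the posterior hard palate, and the effective ratio is effective velar length divided by pharyngeal depth. Correlation between velar length and the ratio is therefore likely. A separate simulation (n = 30, 1000 studies) assumed a correlation of 0.6, with only the ratio truly related to stops:

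| Model | Flags the related feature | Flags the merely correlated feature |
|---|---|---|
| Separate, stops as factor | 50% | 16% |
| Separate, stops linear | 84% | 35% |
| Joint, stops as response | 64% | 5% |

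The joint model holds the merely correlated feature at the nominal rate, at some cost in power for the related one.

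**5. Binary response**

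In the same simulation, a linear model fitted to yes/no LVP continuity put about 6% of fitted values outside 0 to 1.

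**The case against.** **Association has no direction.** Aim 2 speaks of association, and the Abstract describes the analysis in that sense. A reader might infer from the reversal that the plan cannot address Aim 2 at all. The documents do not support that: a one-feature association is still tested, and with stops as a single linear term the test is the same as in the other direction. This stands, but it does not supply mutual adjustment, a suitable model for LVP continuity, or an estimate of the procedure difference in stops.

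**Coding is not stated.** The article never says that stops will be split into seven levels. Grouping or a numeric term is possible, so the sparse-cell argument is conditional. Nor is the contrast of 29% with 64% the gain from the fix. A linear stand-in for the joint model gave 42% for the truly related feature at n = 27 (features correlated 0.6, planned covariates).

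**Software will fit a binary response.** True: the result is a linear probability model. LVP continuity is unsuited to ANCOVA as a dependent variable, not impossible to analyse.

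**Procedure type.** The hypothesis can be read as saying that the anatomical features are unrelated to procedure, which the ANCOVA would address. The other reading, that stops do not differ by procedure, fits Expected Findings, which promises a comparison of speech function across repair techniques using stop production. The ANCOVA does not serve that comparison. A reader might also infer that absence of association will be declared from a non-significant test; no section says so.

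**Exploratory pilot.** This excuses low power, and Strengths and Limitations admits reduced ability to detect subtle effects. It does not excuse a model that contradicts the declared outcome.

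**Conclusion.** The point holds as an inconsistency in the stated text. Stop diversity is the Aim 2 primary outcome in one section, an explanatory term in the only Aim 2 model, and attached to the secondary outcome by label. This rests on the wording alone and needs no assumption.

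Three consequences hold under any coding of stops: no mutually adjusted estimates, no estimate of the procedure difference in stops, and a binary dependent variable in an ANCOVA. In the illustration, the first means that a merely correlated feature is flagged in 16% to 35% of studies instead of 5%. That range depends on the assumed 0.6 correlation and effect sizes.

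The loss of power is conditional. It is large if stops are a seven-level factor (up to 14 cells for about 27 to 30 children) and absent if they are one linear term. It depends on an assumed latent correlation of 0.5 and on the 16-month distribution carrying over to 18 months.

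**What to change.** Replace the Aim 2 ANCOVA with one regression whose response is the number of distinct oral stops (0 to 6) at 18 months.

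- Use a model suited to a bounded count. Ordinal, binomial out of 6, or linear with robust errors would each serve; the choice is partly preference.
- Enter velar length, effective velopharyngeal ratio, LVP continuity and procedure type together as predictors.
- State which of the covariates now listed (sex, cleft type, developmental and language scores) are kept. With about 27 to 30 children the full list is heavy.
- Report each estimate with a 95% confidence interval, including the one for procedure type.
- Make the primary and secondary labels agree between Evaluation Outcomes and Statistical Analysis.

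The cost is one rewritten paragraph and the matching analysis code. No new data are needed; as of April 4, 2026, 8 participants were enrolled and analysis had not begun. The small downside is that joint estimates of correlated features will be less precise than one-at-a-time tests.

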Anatomical restoration is the very premise for current surgical approaches to cleft palate repair. One goal is to create a tension-free closure of the cleft to improve healing and reduce the risk of reopening (ie, palatal fistula [6]). For clefts involving the soft palate, surgery should include reconstruction of the levator veli palatini (LVP) muscle. The LVP muscle, which functions to elevate and retract the soft palate, assists in the closure of the velopharyngeal port. Both intravelar veloplasty (IVV) and Furlow double-opposing Z-plasty (DOZ) are widely used techniques to reconstruct the LVP muscle [6]. IVV focuses on levator sling reconstruction with retropositioning and transverse reorientation of the muscles, whereas DOZ combines levator muscle repositioning with soft palate lengthening through opposing Z-plasty flaps. A systematic review by Timbang et al [7] found that outcomes following cleft palate repair vary by cleft type, with DOZ associated with lower rates of secondary velopharyngeal surgery compared with IVV. One way of reducing tension is to base the surgical plan on patient anatomy, where the surgeon determines procedure type based on the perceived tension of the palatal tissue in the operating room; as DOZ requires overlap of the LVP muscle bundles, it can produce a greater amount of tension on the incision site [7]. Beyond the surgeons’ informal assessment of tension intraoperatively, we do not know whether the child’s presurgical anatomy plays a role in their postrepair outcome, and there is no data-driven approach to choosing one surgical technique over another.

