### Surgical Considerations

Participants will undergo primary palatoplasty within a typical early palate repair window prior to 15 months [38]. Two standard surgical approaches will be evaluated: IVV and Furlow DOZ. These 2 procedures are commonly used for primary palatoplasty at the study site. Due to the observational nature of this study, no standardization or changes to the surgeons’ procedures will take place; however, individual variability will be accounted for by recording the operating surgeon of each participant and controlling for any significant differences between surgeons in the analysis. Both procedures aim to restore the LVP “sling” to its intended anatomical position in the posterior velum but differ in technique. IVV reorients the muscle bundles end to end without overlap and closes the mucosa with a straight-line suture. DOZ repositions the LVP muscle via opposing Z-shaped incisions, lengthening the velum and creating overlap of the muscle bundles. All surgeries will be performed at a single institution by 1 of 5 operating surgeons. Procedure selection and the use of tissue adjuncts will be determined intraoperatively based on the surgeon’s clinical expertise, which may include a perceptual assessment of the amount of palatal tissue and/or tension upon closure of the cleft defect; no randomization will be performed. Tissue adjuncts, in this context, refer to flaps or grafts added to the palate from an alternate location in the mouth (eg, buccal fat pad flap or buccal myomucosal flap).

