**Figure 2 figure2:**
[figure not shown]
Presurgical magnetic resonance image of an infant labeled with cleft palate with cleft width (A) and levator veli palatini (LVP) muscle length (B).

Through aim 2, we will compare velopharyngeal function for speech among infants with repaired cleft palate following different repair techniques using both perceptual (oral stop production) and objective (anatomical) measures of the velopharynx [29,31]. Given that surgery is an anatomical solution to a physiological concern (aberrant speech), it is essential to establish a link between anatomy and physiology in infants and toddlers to facilitate early diagnosis and remediation of VPI in this population. We further hypothesize that anatomical parameters such as a longer velum, greater effective velopharyngeal ratio, and continuity of the LVP muscle (Figure 3) may be associated with greater diversity of oral stop consonants by 18 months. If this hypothesis is accurate, postoperative anatomy of children with repaired cleft palate could be used as a complement for speech production when it comes to considering secondary surgical intervention. Identifying the relationship between postoperative anatomy and velopharyngeal function in toddlers offers a critical opportunity to intervene earlier and improve speech outcomes in this population. These multidimensional data may provide additional confidence in referring for secondary surgical intervention at an earlier age, when speech production is more limited in clinical visits.

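### Aim 2's surgical-type contrast in postsurgical anatomy is not adjusted for the presurgical cleft width and LVP muscle length that Aim 1 expects to predict the choice of procedure

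*Protocol article*

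**What the plan says.** **The Aim 2 model.** The Statistical Analysis section specifies a two-way analysis of covariance on "effects of surgical type and number of oral stops on postsurgical anatomical measures, controlling for sex, cleft type, and developmental and language scores". The outcome is postsurgical anatomy, surgical type is one of two factors, and the covariates are listed by name.

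**How the procedure is chosen.** Surgical Considerations says the surgeon's expertise settles the choice in the operating room, and describes it as one "which may include a perceptual assessment of the amount of palatal tissue and/or tension upon closure of the cleft defect; no randomization will be performed". The Background explains why tension may matter: "as DOZ requires overlap of the LVP muscle bundles, it can produce a greater amount of tension on the incision site".

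**What Aim 1 expects.** The stated hypothesis is that "preoperative cleft width and LVP muscle length are predictive of surgical procedure selection based on intraoperative tension of palatal tissue". Evaluation Outcomes names the same two measures as the predictors, and Expected Findings says they may be predictive.

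**Other adjustment.** Surgical Considerations also promises to record the operating surgeon, "controlling for any significant differences between surgeons in the analysis".

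**Intended use.** Under Expected Findings in the Discussion, the Aim 2 paragraph says "we will compare velopharyngeal function for speech among infants with repaired cleft palate following different repair techniques".

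**Availability.** Study Design and Data Collection schedules a presurgical MRI in the same infants, within two weeks before the repair.

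**The concern.** The two aims do not fit together. Aim 1 looks for presurgical anatomy that separates infants who receive IVV from those who receive DOZ. Aim 2 then compares the postsurgical anatomy of those two groups as if they had started alike, apart from the listed covariates. The better Aim 1's hypothesis does, the less the unadjusted Aim 2 contrast can be attributed to technique.

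Cleft type is a coarse class and leaves differences in width within each type. Surgeon is adjusted for only where differences prove significant, and that adjustment does not capture how one surgeon selects among patients. Cleft width, measured before the cleft is closed, has no counterpart among the postsurgical measures in Table 1, so no other term in the model stands in for it.

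At stake is the reading of the surgical-type term. A difference could reflect case selection, or a real difference could be masked by it. Strengths and Limitations names sample size and a single hospital with several surgeons, but not confounding by indication. Expected Findings looks ahead to a trial that would match patients to techniques. Confounding of this kind does not shrink as the sample grows, so a larger study using the same model would inherit it.

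**Working it through.** **Covariates against hypothesised determinants of choice.**

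| Hypothesised determinant of procedure (Aim 1) | In the Aim 2 model? | Partial proxy in the plan |
|---|---|---|
| Presurgical cleft width | No | Cleft type; surgeon if significant |
| Presurgical LVP muscle length | No | Surgeon if significant |

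**Sample size.** The Participants section gives 39 enrolled and 30% attrition: 39 × 0.70 = 27.3, so about 27 infants. The plan gives no effect size, SD, alpha or IVV:DOZ split. I assume two-sided 0.05, a within-procedure SD of 1, and a 14:13 split.

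**What Aim 1 would need to see.** Taking cleft width alone and a simple t-test, the smallest observed difference reaching p < 0.05 is t(0.975, 25) × √(1/n₁ + 1/n₂).
- 14:13 split: 2.060 × 0.385 = 0.79 SD
- 19:8 split: 2.060 × 0.421 = 0.87 SD

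These are thresholds for an observed difference. The true difference could be smaller with the hypothesis still true, so the range below starts at 0.4 SD.

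**Apparent procedure effect when the true effect is zero.** Let *d* be the difference in cleft width between procedures and *r* the within-procedure correlation of width with the postsurgical measure. The apparent effect is |*r*| × *d*. Its noncentrality is |*r*| × *d* / 0.385, and the rejection rate follows from the noncentral t distribution with 25 degrees of freedom.

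| *d* (SD) | *r* | Apparent effect (SD) | Noncentrality | False-positive rate |
|---|---|---|---|---|
| 0.4 | -0.3 | 0.12 | 0.31 | 6% |
| 0.4 | -0.5 | 0.20 | 0.52 | 8% |
| 0.8 | -0.3 | 0.24 | 0.62 | 9% |
| 0.8 | -0.5 | 0.40 | 1.04 | 17% |
| 1.2 | -0.3 | 0.36 | 0.93 | 15% |
| 1.2 | -0.5 | 0.60 | 1.56 | 32% |

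At *r* = -0.1 the rate stays between 5% and 6% throughout.

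**With the planned covariates in the model.** I simulated 27 infants (4,000 runs per setting) with stop count, sex, cleft type and two scores as covariates. The other covariates were unrelated to the outcome.
- Cleft type unrelated to width: 6% (*d* = 0.4, *r* = -0.3) to 27% (*d* = 1.2, *r* = -0.5).
- Cleft type moderately related to width: 6% to 20% over the same range, so it removes part of the bias only.
- Cleft width added: about 5% in every setting, with the apparent effect within about 0.01 SD of zero.

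**Both measures influencing choice.** A second simulation used 30 infants, odds ratios for choice of 2 to 3 per SD of each measure, and effects of each on the outcome of 0.3 to 0.5 SD per SD. The planned covariates gave a false difference of 0.33 to 0.76 SD and 12% to 48% false positives. Adding both presurgical measures brought this to 4.5% to 5.5%. With an odds ratio of 1 (choice unrelated to anatomy) the rate was about 5% either way.

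**The case against.** **The plan only hypothesises the link.** It does not say that cleft width and LVP length determine the choice, and Expected Findings allows for there being no anatomical link. This stands. If choice does not depend on this anatomy there is no bias, so the point is conditional.

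**Aim 2 is not a comparison of techniques at heart.** Its question is which postsurgical features go with stop diversity, in an exploratory observational pilot. This also stands: procedure is one factor, and no causal claim of superiority is made. But it is a named factor, and a comparison between techniques is announced.

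**Stronger readings.** A reader might infer that the omission also makes DOZ look better for speech, or defeats the part of the Aim 2 hypothesis that stop diversity is unrelated to procedure type. The documents do not support that. The quoted model has anatomy as its outcome and stop count as a factor, so its surgical-type term does not test speech against procedure. The speech comparison in the Discussion has no stated covariate list to fault. Nor are sex, cleft type and the scores the only adjustment, since surgeon is conditionally controlled.

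**The size is assumed.** No correlation or group difference is in the documents, and mild assumptions give only 6% to 7%. A zero effect is also an odd null for velar length, since Surgical Considerations describes DOZ as lengthening the velum. The figures are an illustration of the mechanism only.

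**An SAP may cover it.** The article prints the covariates as a specific list, so this is a stated choice and not a detail left open.

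**Conclusion.** The point holds in conditional form. If presurgical cleft width and LVP length predict procedure, as Aim 1 hypothesises, and also affect postsurgical anatomy, the surgical-type contrast in the Aim 2 model can be confounded by indication in either direction. The planned covariates and the conditional surgeon adjustment reduce this only in part.

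Under the stated assumptions (about 27 infants, no true effect, width difference 0.4 to 1.2 SD, correlation -0.3 to -0.5) the 5% error rate becomes roughly 6% to 30%, and adjusting for cleft width restores about 5%. The actual size cannot be known from the documents. The stops-anatomy association, which is the main Aim 2 question, is not what this point challenges.

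**What to change.** Keep the planned Aim 2 model and all its prespecified covariates. For the surgical-type contrast, and for any IVV-DOZ comparison made as the Discussion announces:

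- Prespecify an additional analysis adjusted for presurgical cleft width. Add LVP muscle length, or use a single component combining the two, if degrees of freedom allow.
- Report the crude and adjusted contrasts side by side, with the standardised IVV-DOZ difference in each presurgical measure.
- Describe the contrast as one between selected groups, and list confounding by indication among the limitations.

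Keeping this as a separate analysis leaves the stops-anatomy question unconditioned on baseline anatomy, and no developmental or language score has to be given up.

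**Cost.** This is a change of plan wording. The scans are already scheduled, and the article reports 8 infants enrolled and no analysis begun. The added analysis uses 1 to 2 degrees of freedom, and infants without a usable presurgical scan are dropped or imputed in it.
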